## Abstract

**Background:**

Recent guidelines for the management of hypertension focus on treating patients according to their global cardiovascular risk (CVR), rather than strictly keeping blood pressure, or other risk factors, below set limit values. The objective of this study is to compare the effect of a simple versus a complex educational intervention implementing this new concept among General Practitioners (GPs).

**Methods/design:**

A prospective longitudinal cluster-randomised intervention trial with 94 German GPs consecutively enroling 40 patients each with known hypertension. All GPs then received a written manual specifically developed to transfer the global concept of CVR into daily General Practice. After cluster-randomisation, half of the GPs additionally received a clinical outreach visit, with a trained peer discussing with them the concept of global CVR referring to example study patients from the respective GP. Main outcome measure is the improvement of calculated CVR six months after intervention in the subgroup of patients with high CVR (but no history of cardiovascular disease), defined as 10-year-mortality ≥ 5% employing the European SCORE formula. Secondary outcome measures include the intervention's effect on single risk factors, and on prescription rates of drugs targeting CVR. All outcome measures are separately studied in the three subgroups of patients with 1. high CVR (defined as above), 2. low CVR (SCORE < 5%), and 3. a history of cardiovascular disease. The influence of age, sex, social status, and the perceived quality of the respective doctor-patient-relation on the effects will be examined.

**Discussion:**

To our knowledge, no other published intervention study has yet evaluated the impact of educating GPs with the goal to treat patients with hypertension according to their global cardiovascular risk.

**Trial registration:**

ISRCTN44478543

## Background

### Hypertension management and global cardiovascular risk

Arterial hypertension is a major risk factor for cardiovascular diseases (CVD) such as myocardial infarction and stroke. The detection and treatment of elevated blood pressure (BP) and the management of patients with hypertension is an important challenge of daily practice in primary care. Previous studies found that only 60% of patients with known hypertension receive treatment, and in fewer than 50% of treated patients BP was controlled below 140/90 mmHg [1-3].

However, recent guidelines on hypertension [4-6], and on both primary and secondary cardiovascular prevention [7] emphasise that rather than to focus on single risk factors, intensity of care should focus on the global cardiovascular risk (CVR) of an individual patient. Global cardiovascular risk is an arithmetical compound of age, sex, and the known cardiovascular risk factors, and can be approximated by means of various risk calculators. If pharmacological risk factor treatment promises a relative risk reduction of some 25% [8,9], or possibly up to 80% in combination therapy [10], then a *relevant *absolute risk reduction is only possible where there is a relevant absolute risk to begin with. According to the concept of global cardiovascular risk, therefore, pharmacological treatment is only recommended for patients with a cardiovascular 10-year-mortality at or above 5%. The essence of this paradigmatic change is that treatment efforts and resources should be concentrated on where the (high) cardiovascular risk is: "treat risk, not risk factors" [11]. For general practitioners (GPs), this concept is of particular interest because it firstly focuses efforts and resources on high-risk patients, secondly makes GPs and patients more flexible in the choice of risk-lowering interventions, and thirdly reassures patients with low CVR that they may not benefit from treatment despite possible elevated risk factor levels.

### Implementing the concept of global CVR for the treatment of patients with hypertension

Few studies have been reported [12,13] addressing hypertension management in primary care with explicit consideration of global cardiovascular risk, none of them from Germany, and none of them measuring CVR before and after the intervention. The little available data suggest that GPs are not familiar with the new concept of global cardiovascular risk [14,15].

Initiating a process of behavioural change concerning guideline adherence of physicians is a challenge. Systematic reviews of interventions to change professional practice show that passive dissemination of information has little or no effect [16]; combined interventions using audits and feedbacks yield a larger impact, and clinical outreach visits seem to bring about the largest observed changes [17]. Outcomes are better if interventions include active and passive elements of learning, and if they use individual face-to-face interactions [18].

### Objective and research questions

Our general objective is to demonstrate that GPs who have been made familiar with the concept of global CVR by means of a complex, tailored intervention will adapt their treatment accordingly, resulting in measurable changes in patients' clinical outcomes. In particular, these are our questions:

1. In a subgroup of patients with high CVR (but no history of CVD), does a complex educational intervention directed at the GPs, including an educational outreach visit, lead to a higher improvement of mean CVR than a passive intervention, i.e. posting a manual?

2. What are the differential effects of the two interventions on various clinical targets in three risk-defined subgroups of patients with hypertension, namely patients with (i) a history of CVD, (ii) high CVR, but no history of CVD, and (iii) low CVR?

3. Are the results influenced by patient age, sex, or social status, or by the perceived quality of the respective doctor-patient-relationship?

In order to gain a deeper understanding of possible outcomes and their background, we also conducted an embedded qualitative study, employing semi-structured expert interviews in order to explore GPs' views and attitudes towards the new global CVR concept. The corresponding study protocol and its results will be published elsewhere.

## Methods/Design

### Ethics and Registration

Approval was granted by the Ethics Committee of the medical faculty of the University of Duesseldorf (no. 2715). Patient consent was not deemed necessary by the Committee since we use anonymous data routinely collected by GPs.

The trial was registered at ISRCTN44478543.

### Design

Prospective non-blinded longitudinal cluster-randomised intervention study. One GP (or one group practice with 1–3 GPs, respectively) represents a cluster, whereas the patients are the observation units.

After enrolling the patients, GPs were cluster-randomised into two groups, A and B. GPs of group A received a written manual by mail explaining the concept of global CVR. In addition, the GPs of this group received a tailored intervention including a clinical outreach visit (for details cf. *Intervention*). GP's of group B received only the written manual by mail with no further educative intervention.

Thus, the complex intervention (group A) is not compared to usual care, but to a low-level intervention (group B). This reflects our hypothesis that the benefit of the complex and therefore more-costly intervention may be relevant only if the effect can be demonstrated against a less-complex, low-cost intervention.

Figure 1 is a flow chart of this two-group intervention trial.

**Figure 1 F1:**
[figure not shown]
Flowchart.

### Calculation of cardiovascular risk

Global CVR is calculated employing the European SCORE formula, modified by factor 2 or 3 for men and women, respectively, with diabetes. We follow the SCORE working group's definition of a 10-year cardiovascular *mortality *< 5% for "low" risk, and ≥ 5% for "high" risk in patients with no history of cardiovascular disease, corresponding with the 20% dividing line commonly used in cardiovascular *morbidity *tables [19]. We opt for the SCORE rather than for the Framingham or PROCAM [20] risk tables because they are based on data for both men and women, and retrieved from recent national (German) cohort studies.

### Anticipated dropouts and sample size calculation

Sample size calculation refers to research question 1 (see above). In order to demonstrate an effect of reducing mean calculated CVR by a tenth in the subgroup of patients with high CVR (SCORE ≥ 5%, no history of cardiovascular disease) with a power of 80%, we calculated a necessary initial sample size of 2 × 51 recruited GPs enrolling 40 patients each. We estimated a GP drop out during the enrolment phase of 5%, a patient enrolment rate of 95%, a GP drop out between baseline and follow up of a further 5%, and a patient drop out between baseline and follow up of 10% (resulting in 3146 patients enrolled by 92 GPs). The sample size calculation was based on the assumption of a standard deviation of 0.44 for the CVR changes on the log-odds scale, an intra-class correlation of 0.2 and a proportion of 40% high risk patients in the total sample, the latter derived from a pilot study with 330 patients cared for by 20 GPs. According to these assumptions, 2 × 816 patients were required for the primary analysis in the high risk group.

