### Statistical analysis

The primary analysis includes all randomised patients of group II with global CVR determinations at baseline (ITT population). CVR values at baseline as well as at follow-up will be transformed on the log-odds scale (multiplicative model). In case of missing follow-up values, a LOCF (last-observation carried forward) imputation will be performed, i.e. the baseline determination will be imputed as follow-up determination. For the primary analysis, a two-level random coefficient model will be fitted to the data with patients nested in physicians modeled as random effects. This model takes the correlation structure resulting from cluster randomisation into account and allows for differences between physicians in treatment effects. The primary analysis will compare the baseline-adjusted follow-up means between random groups at a significance level of 0.05, two-sided.

As sensitivity analyses, calculations will be repeated for the complete cases population and for a dataset with missing values imputed using an EM algorithm.

Secondary analyses will be in the complete cases only. Analogous to the primary analysis, mixed models will be fitted for the secondary endpoints in group I, group II and group III separately.

In the exploratory part of the analysis, the covariates age, sex, social status, and perceived quality of the respective doctor-patient-relationship will be added as confounders and potential effect modifiers to the statistical model. By backward selection, optimal models will be identified and reported.

Calculations will be performed with SPSS and STATA, last available versions.

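### The sample size paragraph's counts do not fit together, and its 80% power is not reproduced at two-sided 0.05 for most mean CVR values one might assume

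*Protocol article*

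**What the plan says.** All figures are in the protocol article.

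- **Anticipated dropouts and sample size calculation.** The target is "an effect of reducing mean calculated CVR by a tenth in the subgroup of patients with high CVR", and "with a power of 80%, we calculated a necessary initial sample size of 2 × 51 recruited GPs enrolling 40 patients each". Four losses are assumed: 5% of GPs during enrolment, a 95% patient enrolment rate, a further 5% of GPs before follow-up, and 10% of patients before follow-up. The outcome of these is given as "resulting in 3146 patients enrolled by 92 GPs". The variance inputs are "a standard deviation of 0.44 for the CVR changes on the log-odds scale" and an ICC of 0.2, with 40% of patients at high risk. The closing sentence is "According to these assumptions, 2 × 816 patients were required for the primary analysis in the high risk group". The paragraph gives no significance level, no sidedness and no mean CVR for the high-risk group.
- **Statistical analysis.** "The primary analysis will compare the baseline-adjusted follow-up means between random groups at a significance level of 0.05, two-sided". The ITT set is every randomised high-risk patient with a baseline CVR, and a missing follow-up value is replaced by the baseline value.
- **Abstract, Methods/design.** The trial is described as having 94 GPs, so recruitment appears settled.

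**The concern.** A number called the requirement for the primary analysis should be net of expected losses. The gross number to recruit should then be inflated so that the net number is reached. Here the closing figure appears to be the gross count, while the paragraph's own losses bring the expected net count well below it. The label on 3146 is also doubtful, because two of the four losses behind it occur after enrolment.

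This is the only power justification for research question 1. If the result is not significant, readers will judge how informative it is partly from the stated 80%. If that figure holds only under an unstated assumption, or under a test other than the one planned, they should be told.

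**Working it through.** **1. The plan's own counts**

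- GPs: 102 × 0.95 × 0.95 = 92.06, i.e. 92 as stated.
- Patients per remaining GP: 40 × 0.95 × 0.90 = 34.2.
- Patients: 92 × 34.2 = 3146, as stated. This includes both losses between baseline and follow-up, so it counts patients with follow-up.
- Enrolled: 102 × 0.95 = 96.9 GPs; 96.9 × 40 × 0.95 = 3682 patients.
- High risk, no loss: 51 × 40 × 0.40 = 816 per arm, exactly the stated figure.
- High risk, enrolled (ITT set): 3682 × 0.40 / 2 = 736 per arm.
- High risk, with follow-up: 3146 × 0.40 / 2 = 629 per arm, 23% below 816 (1 − 629/816).

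**2. Effect on the log-odds scale**

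A one-tenth reduction of a mean CVR p is δ = logit(p) − logit(0.9p). The document gives no p, so the values used are assumptions: δ = 0.1106 (p = 5%), 0.1164 (10%), 0.1229 (15%), 0.1301 (20%). If the effect is read as an odds ratio of 0.9, δ = −ln(0.9) = 0.1054.

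**3. Standard error and power**

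For m high-risk patients per GP and n per arm:

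- Design effect: DE = 1 + (m − 1) × 0.2
- SE = 0.44 × √(2 × DE / n)
- Two-sided power ≈ Φ(δ/SE − 1.96)

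After dropout, m = 34.2 × 0.40 = 13.68, DE = 3.536, n = 629 and SE = 0.0466. At p = 10%, δ/SE = 0.1164/0.0466 ≈ 2.50 and the power is 70%. With no loss, m = 16, DE = 4, n = 816 and SE = 0.0436.

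| Effect assumption | No loss (2 × 816), two-sided | After dropout (2 × 629), two-sided | After dropout, one-sided 0.05 |
|---|---|---|---|
| ln(0.9) | 68% | 62% | 73% |
| mean CVR 5% | 72% | 66% | 77% |
| mean CVR 10% | 76% | 70% | 80% |
| mean CVR 15% | 81% | 75% | 84% |
| mean CVR 20% | 85% | 80% | 87% |

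Two-sided 80% needs a mean CVR of about 14% with no attrition, or about 20% after the planned dropout.

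**4. The ITT set with LOCF**

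Here n = 736, m = 15.2, DE = 3.84 and SE = 0.0449. A share of 0.95 × 0.90 = 0.855 of these patients has a real follow-up value; the rest are assigned no change, so the expected difference is 0.855 × δ. With SD 0.44 unchanged, two-sided power is 52% for ln(0.9) and 56%, 60% and 65% at mean CVR 5%, 10% and 15%. If the SD is also shrunk, by √0.855, the range is 58% to 72%.

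**5. Reduction detectable with 80% power, two-sided**

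δ must equal (1.96 + 0.84) × SE, divided by 0.855 under LOCF. SD is 0.44 throughout.

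- Complete cases: δ = 0.1307, a reduction of 11.7%, 11.2% or 10.6% at mean CVR 5%, 10% or 15%.
- ITT with LOCF: δ = 0.1472, a reduction of 13.1%, 12.5% or 11.9%.

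**The case against.** **The power figure depends on an assumed mean CVR.** This stands. The document gives none, so no single percentage can be presented as the trial's power. Only the range can be reported.

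**The planned analysis adjusts for baseline, whereas 0.44 is the SD of changes.** This stands in part. If baseline and follow-up variances are equal, adjustment multiplies the variance by (1 + r)/2, where r is their correlation. At mean CVR 10%, the 2 × 629 power would be 82%, 80% or 75% for assumed r of 0.5, 0.6 or 0.8. Equivalently, an SD of about 0.39 would give 80%. The document states no r and claims no such gain, so this could close some or all of the gap but cannot be counted.

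**LOCF keeps dropouts in the analysis.** True, so 629 is not the size of the ITT set. But 736 is still below 816, and imputing no change costs more power than the extra patients add.

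**Dropout may have been allowed for.** A one-sided 0.05 calculation at mean CVR 10% gives 80% with the post-dropout numbers. The article also calls 2 × 51 GPs an initial sample. On that reading 816 is only mislabelled, but the sidedness then conflicts with the analysis section.

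A reader might therefore infer that the authors forgot dropout and that the trial has about 70% power. The document supports neither as fact. The first is one of two possible causes, and the second holds only for complete cases, a mean CVR near 10% and no gain from adjustment.

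**Conclusion.** The inconsistency in the counts is certain and needs no outside figure. The 816 is a pre-loss count, the plan's losses give 629 with follow-up or 736 in the ITT set, and 3146 is not the number enrolled. If 816 were truly the net need, 2 × 51 GPs would be too few.

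The power conclusion is conditional. On SD 0.44, ICC 0.2, equal cluster sizes, two-sided 0.05 and no gain from baseline adjustment, power after dropout is 62% to 75% from ln(0.9) to a mean CVR of 15%. It reaches about 80% only near a mean CVR of 20%, four times the 5% threshold that defines high risk. Under LOCF with the SD unchanged the corresponding range is 52% to 65%. The cause cannot be determined from the document.

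This should be fixed, but it does not threaten the design. For complete cases, the reduction detectable with 80% power moves from the stated 10% to about 11–12% at mean CVR 5% to 15%. No endpoint or analysis has to change.

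**What to change.** Rewrite the sample size paragraph, without enrolling more GPs:

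1. Label 3146 as the expected number of patients with follow-up, and give about 3682 as the number enrolled.
2. Replace 2 × 816 with the expected high-risk numbers: about 2 × 736 enrolled and about 2 × 629 with follow-up.
3. State the mean CVR assumed for the high-risk group, the significance level and sidedness used in the calculation, and any reduction in SD expected from baseline adjustment. If the calculation was one-sided, say so and reconcile it with the two-sided test.
4. Give the two-sided power, or the reduction detectable with 80% power, both for the ITT analysis with LOCF and for complete cases.

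The cost is one reworded paragraph and a short recalculation. The downside is that, unless a documented gain from baseline adjustment or a high mean CVR supports the 80%, the stated power becomes less favourable.

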### Participants and randomisation

We recruited GPs in the district of North-Rhine, choosing three circumscribed regions close to the cities of Düsseldorf, Cologne, and Aachen, one region for each of the three attending peers (convenience sample).

A random sample of the registered GPs in a given postal code were invited to participate by fax, and called 3–5 days later by one of the three trained peers. Incentives to participate were 1. the offer of a free and pharma-independent manual and, depending on randomisation, possibly peer training in a relevant field of General Practice; 2. the opportunity to take part in an innovative research project developed by GPs for GPs; and 3. an honorarium of € 300 for completing both data surveys (requiring a net time investment of 5 to 6 hours).

After patient enrolment and baseline data collection, the GPs (clusters) were randomised to intervention groups A and B.

In order to avoid the possibility that GPs already familiar with the concept of global CVR were accidentally over-represented in either group, we asked the GPs to estimate the individual CVR of each patient they enrolled. We compared this estimate with the respective patients' calculated CVR, and divided the GPs into two groups, according to whether their estimate is close to or far from the calculated CVR. We assumed this division to approximate a measure for *familiarity with the concept of global CVR*, and for randomisation, GPs were stratified by this attribute.

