### Intervention

In order to address the complex issue of hypertension management in the light of absolute cardiovascular risk, we developed a multi-faceted intervention through a process of identifying barriers to implementation, e.g. comprehensibility of the new concept, and communication pitfalls. We compiled a written manual (17 pages) on the basis of the ESC-Guidelines [7] with the following chapters:

1. Introduction.

2. What is new about the "concept of global CVR?"

3. How to determine global CVR?

4. What is the likely individual benefit of the treatment of cardiovascular risk factors?

5. Two examples of decision-making.

6. Non-pharmacological therapy: motivation for behavioural change and psychosocial support.

7. Pharmacologic treatment with antihypertensive drugs.

8. Pharmacologic treatment with lipid-lowering drugs.

9. Literature.

This manual was sent by mail to all GPs (randomisation groups A and B). In addition, GPs in group A received a personal intervention including an outreach visit by a peer (30–45 min.), a feedback telephone call after three weeks (5–10 min.), and delivery of a block of 50 patient information sheets. Thus, we compared the effect of an elaborate intervention (A) with the conventional process of postal dissemination of a guideline-based manual (B), which is generally assumed to have no or little significant effect on physician behaviour [16].

During the outreach visit, peer and GP discussed the new concept on the basis of (a) our manual and (b) 3–4 suitable cases selected by the peer from this GP's baseline data. The cases were chosen to include at least one patient with a history of CVD, and at least two patients without such a history; of the latter one at low risk (SCORE < 5%), and one at high risk (SCORE > 5%), respectively. The discussion of the GPs' respective patient cases included feedback elements, and served as concrete examples to demonstrate the paradigmatic changes of the CVR concept to the GP. Furthermore, the GPs were instructed how to use the SCORE calculator of global cardiovascular risk (print version, included in the manual), and additional patient information sheets.

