Three practising GPs ([name]) were trained to explore GPs' understanding, beliefs, and attitudes during the initial phase of the conversation in order to tailor the concept's message to the individual colleague they were talking to. The process of standardisation was facilitated by a dialogue draft for the outreach visit, regular audit-meetings, and personal feedback from a passive observer who attended the first three visits of each peer.

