### Data Retrieval and Monitoring

Every GP received instruction on study procedures individually by one of the three peers. At baseline, data sheets were directed to GPs only, but at follow-up there were different data sheets for practice nurse and GP, respectively, restricting the workload of the GPs to data only they could provide. Data sheets were personally collected by the peers at baseline, and sent by mail by the GPs at follow-up. Data were entered into electronic sheets by medical students. Practice nurses or, where necessary, GPs were contacted if inconsistencies occurred or to complete missing data.

In order to monitor the quality of the data submitted by the GPs at baseline, at the end of the study we issued a data sheet to the practice nurses requiring them to re-enter the baseline data for blood pressure and cholesterol from the electronic record. Since the written baseline data sheets had been collected from the GPs, we regarded it as unlikely that the nurses or GPs would recall after follow up what numbers had been entered at baseline. We will examine the congruence of the data documented by the GPs on the baseline forms with the data referring to the same calendar day entered by the practice nurses some 6–9 months later.

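### Region, which is the same variable as peer, is missing from the stated primary model; this costs a little precision but does not bias the comparison

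*Protocol article*

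**What the plan says.** Protocol article, Participants and randomisation: recruitment took place in one district by "choosing three circumscribed regions close to the cities of Düsseldorf, Cologne, and Aachen, one region for each of the three attending peers (convenience sample"). Invited GPs were then "called 3–5 days later by one of the three trained peers". The GPs were randomised after patient enrolment and baseline data collection, stratified by how close their own risk estimates came to the calculated ones. No other stratum is named.

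Data Retrieval and Monitoring: "Every GP received instruction on study procedures individually by one of the three peers", which covers both arms. "Data sheets were personally collected by the peers at baseline"; the GPs had completed the sheets, and the peers picked them up.

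Intervention: "GPs in group A received a personal intervention including an outreach visit by a peer (30–45 min".). The peer also chose the example cases for the visit. The peers had been "trained to explore GPs' understanding, beliefs, and attitudes during the initial phase of the conversation in order to tailor the concept's message", so each visit was adapted to its GP. The same section describes standardisation through a dialogue draft, regular audit meetings and a passive observer at each peer's first three visits.

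Statistical analysis: "a two-level random coefficient model will be fitted to the data with patients nested in physicians modeled as random effects". The comparison is adjusted for baseline, and the model is said to allow treatment effects to differ between physicians. The exploratory covariates are age, sex, social status and perceived quality of the doctor-patient relationship. Region or peer appears in none of these places.

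**The concern.** With one region per peer, region and peer cannot be told apart. The natural reading is that each region's own peer called, instructed and (in group A) visited its GPs, although the article does not say so task by task. Regions may differ in how practices change treatment over six months, and peers may differ in how they instruct GPs or conduct a deliberately tailored visit. Either difference makes GPs in the same region resemble one another.

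The stated model has no place for this. Regional variation stays in the physician-level variance, and with an assumed intra-class correlation of 0.2 that variance dominates the standard error of a cluster-randomised comparison. What is at stake is precision that a known GP-level variable could recover, and clarity about which peers the result describes.

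**Working it through.** **Inputs** (Protocol article, Anticipated dropouts and sample size calculation): 2 × 51 GPs with 40 patients each; GP losses of 5% and 5%; patient enrolment 95%; patient loss 10%; SD of change 0.44 on the log-odds scale; ICC 0.2; 40% high-risk patients.

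**The plan's own figures.** GPs: 102 × 0.95 × 0.95 = 92, or 46 per arm. Patients: 92 × 40 × 0.95 × 0.90 = 3146. Both match the article. High-risk patients per GP: 40 × 0.95 × 0.90 × 0.40 = 13.68. (The stated 2 × 816 equals 51 × 40 × 0.40 per arm, before losses; that is a separate matter and is not used here.)

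**Standard error without region.**
- Between-GP variance: 0.2 × 0.44² = 0.0387.
- Variance of a GP mean: 0.44² × (0.2 + 0.8/13.68) = 0.1936 × 0.2585 = 0.0500.
- Between-GP share: 0.2/0.2585 = 77%.
- SE of the arm difference: √(2 × 0.0500/46) = 0.0466. With the 94 GPs named in the abstract (47 per arm) it is 0.0461.

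**Gain from adjusting for region.** If region explains a share r of the between-GP variance, adjustment multiplies the SE by √(1 − 0.774r). The share r is assumed.

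| r | SE ratio, adjusted/unadjusted | Unadjusted SE too large by |
|---|---|---|
| 5% | 0.980 | 2.0% |
| 10% | 0.961 | 4.1% |
| 15% | 0.940 | 6.4% |

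The primary analysis carries baseline forward for patients without follow-up. If all 40 × 0.95 × 0.40 = 15.2 high-risk patients per GP are therefore counted, the between-GP share is 79% and the ratios are 0.980, 0.960 and 0.939, practically the same.

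**Bias and type I error.** Simulation at GP level: 94 GPs, 47 per arm, regions of 31, 31 and 32 (sizes assumed), allocation permuted without regard to region, and regional shifts of −s, 0 and +s with s from 0 to 0.2 log-odds. With region left out, the mean estimate stays at its true value and the type I error is 4.5–5.4%. The cost shows only in the SE: at s = 0.1 it is about 0.049 unadjusted against about 0.047 adjusted, a ratio of about 1.06. This agrees with the table, because shifts of ±0.1 have variance (2/3) × 0.1² = 0.0067, and 0.0067/(0.0387 + 0.0067) = 15% of the between-GP variance.

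**Effects by region.** With a third of the GPs, the SE is 0.0466 × √3 = 0.081 and the 95% half-width is 1.96 × 0.081 = 0.16. The target, a reduction by a tenth, is −ln 0.9 = 0.105 on the log scale, so each region's interval extends further than the whole target effect.

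**The case against.** The strongest objection is that nothing here is wrong, only unadjusted. A condensed article need not list every fixed effect, and the sentence describing the model does not mention even the familiarity stratum. The three regions lie in one district and the comparison is already adjusted for baseline, so what remains between regions may be small; no passage supports any particular share. All of this stands, and it keeps the point modest. It does not remove it: the article names the stratum, the levels of the model and the exploratory covariates, so adding region is a specific change to a stated analysis.

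Two stronger readings are tempting, and the documents support neither.

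- A reader might infer that regional imbalance distorts the result unnoticed. Allocation followed enrolment and baseline recording, so regions differ between arms only by chance, and regional noise already enters the SE through the physician variance. The baseline sheets were completed by the GPs before allocation and merely picked up by the peers.
- A reader might infer that the planned interval is too narrow because GPs visited by one peer share that peer's effect. That is so only for inference to peers in general. Its size depends on a between-peer SD that the article does not give, and a fixed main effect for region would not correct it. For these three peers no widening is needed.

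Nor is it right that delivery went unchecked: the audit meetings and observed first visits are checks on it. A table of effects by peer could not replace them. With equally effective peers, chance alone would give at least one region a zero or reversed effect in about 26% of trials, since 1 − Φ(0.105/0.081)  ≈ 0.097 and 1 − (1 − 0.097)³ ≈ 0.26.

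**Conclusion.** The point holds as one of efficiency and scope. Region/peer is a single known three-level variable that the stated strata, primary model and exploratory covariates all leave out. For these three peers the comparison remains unbiased and the type I error nominal. The SE is about 2–6% larger than needed if region explains 5–15% of the between-GP variance; that range is an assumption, and the gain is close to nil if the regions are alike. The calculation also rests on the plan's SD of 0.44, its ICC of 0.2 and 46 GPs per arm. Inference beyond these three peers is a matter of generalisability that the stated model does not address.

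**What to change.** Add region/peer as a fixed effect with three levels to the primary model and to the mixed models for the secondary endpoints, and specify this before the analysis is run. Three peers are too few for a random effect. State in the report that the primary interval applies to these three peers. Arm effects by region may be shown with confidence intervals as description only, with a note that a half-width of about 0.16 against a target of about 0.105 can neither confirm nor refute consistent delivery.

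Cost: two degrees of freedom and, if wanted, one table. Each GP was recruited within one of the three regions, so no new data should be needed. The downside is little or no gain if the regions are alike. Randomisation is reported as done, so no change to the strata is proposed.
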